### Reporting

We will report study findings in accordance with CONSORT and STARI guidelines. We will submit final study results to a peer-reviewed scientific journal for publication and present findings at academic conferences. We will also report study results in the ClinicalTrials.gov registry.

### Sample size calculation

A sample of 79 educators per group, within 26 ECEC centres would be sufficient to detect a 15% improvement relative to control in AP minutes, given an ICC of 0.03, a design effect of 1.06 and an alpha of 0.05 with 80% power [39].

For child outcomes, a similar calculation was performed to estimate the number of children needed to detect a 0.5 standard deviation increase in FMS outcomes with 80% power and an alpha of 0.05. Assuming a 25% attrition rate and that 5 children participate per site at both time points, 92 children per group are needed, which translates to 36 centres. However, since the requirements for educator outcomes are more stringent, 52 centres will be recruited and randomized, and child-level data will be collected at all 52 centres.

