## Methods and materials

### Study design

We will recruit 52 ECEC centres to participate in the RCT between 2023 and 2025 from the Metro Vancouver and Greater Victoria regions of BC, Canada. Recruitment began 10/10/2023, with our first data collection 08/11/2023. We anticipate recruitment will finish 15/05/2025. Data collection is anticipated to be completed 30/09/2025 and our results compiled by 01/03/2026. Centres will be recruited through an initial mail invitation and follow-up phone calls. Upon informed consent of centres meeting inclusion criteria, half will be randomised to receive the intervention immediately while the other half will receive the intervention three months post randomization and act as a standard of care waitlist control group. The experimental group will receive the ATP+ intervention, a capacity-building professional development opportunity designed to support ECEC providers in implementing the best practices for AP. The standard of care waitlist control group has access to publicly available Appetite to Play materials during the three-month waitlist period. The SPIRIT Schedule of enrolment, intervention and assessments is outlined in Fig 1, as well a visual of the study flowchart is presented in Figure 2.

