### Primary outcomes

***Change in AP and FMS practices***: Child engagement in AP and FMS activities (i.e., time spent in AP, time spent in FMS, number of FMS activities, time spent outdoors, number of outdoor sessions, and an index on the number of best practices facility adheres to) will be measured with field observation and self-report. For field observations, we will use a modified version of the Environment and Policy Assessment and Observation (EPAO) tool [27], which captures type of AP and FMS (locomotor, agility, and/or object/control) activity, duration, location (indoor or outdoor), and intensity of movement. The field observations will initially be completed independently by two trained members of the research team and involve one observer once high intra-observer consistency is obtained. The observations will take place for eight hours of the ECEC centre’s operational times (8:30am-4:30 pm), to capture the activities when most children are present at the facility. The self-report evaluation will be based on questions from the Early Years Survey and the EPAO as a Self-Report instrument (EPAO-SR), adapted to specifically assess the practices targeted by the AP standards in BC, such as providing a minimum of 60 minutes outdoor AP time per day, at least 120 minutes of AP per day, and the use of both facilitated and unfacilitated AP activities that cover FMS [27].

***Change in FMS***: Child FMS will be assessed with the Test of Gross Motor Development version 3 (TGMD-3), a validated, norm-referenced tool for assessing 13 gross motor skills in both locomotor and object control categories [28]. A modified TGMD-3 protocol is commonly used in early childhood movement skill interventions [29]. In this study, we will evaluate six skills: gallop, hop, horizontal jump, two-hand catch, kick a stationary ball, and overhand throw. A composite score will be computed for locomotor and ball skills with a gross motor composite score computed for the analyses. The TGMD-3 performances will be videoed by the research team and scored at a later date. Two members of the research team will independently score the children on the TGMD-3 criteria and discrepancies will be discussed with a third reviewer.

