### Randomization

A computer-generated (www.sealedenvelope.com) randomization schedule will be used to allocate participants in blocks of two, four, six, or eight participants with a randomization ratio of 1:1. The allocation schedule will be concealed in the randomization module of REDCap and only assigned after informed consent and baseline assessments have been completed. Research team members and participants are blinded to allocation at baseline. They will not enter or modify the allocation schedule, as it will be entirely computer-generated. After randomization, participants and research team members will not be blinded to the allocation conditions because participants will know whether they receive the ATP+ intervention immediately or in 3 months, and team members will be tasked with providing intervention group participants access to the intervention. Allocation assignment will be concealed from the researchers at the analysis stage.

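### The 80% power for AP minutes is worked out on educators; it does not carry over to AP minutes observed once per centre, where the sample is 26 vs 26

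*Protocol article*

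**What the plan says.** **Sizing.** The Sample size calculation section of the protocol article says "A sample of 79 educators per group, within 26 ECEC centres would be sufficient to detect a 15% improvement", "given an ICC of 0.03, a design effect of 1.06 and an alpha of 0.05 with 80% power". The target is a "15% improvement relative to control in AP minutes"; no control mean or SD of AP minutes is given. The same section puts the child outcome at 36 centres and says the educator outcomes are the more demanding, so that "52 centres will be recruited and randomized, and child-level data will be collected at all 52 centres".

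**Unit of allocation.** Study design says of the centres that "half will be randomised to receive the intervention immediately while the other half will receive the intervention three months post randomization", and Randomization adds "with a randomization ratio of 1:1". That is 26 centres per arm.

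**Measurement.** Primary outcomes lists time in AP, time in fundamental movement skills (FMS), number of FMS activities, time outdoors, number of outdoor sessions, and "an index on the number of best practices facility adheres to". These are measured by field observation and by self-report. On the observation: "The observations will take place for eight hours of the ECEC" centre's operating day. It records type, duration, location and intensity of activity. No record per educator or per room is described.

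**The concern.** The power calculation counts about three educators per centre and treats them as nearly independent. That can describe a questionnaire answered by each educator. It does not describe a day's observation of a centre, which gives the same number of records however many educators enrol.

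The power sentence does not say which of the two sources of AP minutes it covers. A reader will naturally apply the 80% to the observed measure, which is the one that does not depend on unblinded staff reporting on their own practice. If the observed comparison came out null, it could then be read as fair evidence of no effect when the design may have had little chance of detecting the stated 15% difference. The trial's size also rests on this one calculation.

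**Working it through.** **Inputs from the protocol article:** 79 educators per group; 26 centres per arm (52 randomised 1:1); ICC 0.03; design effect 1.06; alpha 0.05; power 80%; target 15% relative difference. **Assumed here:** two-sided alpha (sidedness is not stated) and a two-sample t-test.

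**1. Reproduce the design effect.** Educators per centre: 79/26 = 3.04. Design effect = 1 + (m − 1) × ICC = 1 + (3 − 1) × 0.03 = 1.06, as stated. This confirms that the 26 centres are per arm: 13 per arm would give m = 79/13 = 6.08 and a design effect of 1.15.

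**2. Back-solve the standardised difference.** The 79 cannot be derived from the stated inputs, because there is no SD. Working backwards, the effective n per arm is 79/1.06 = 74.5. By the normal formula, d = (1.960 + 0.842) × √(2/74.5) = 0.459; by the t-test, d = 0.462. The implied SD for a 15% difference is 0.15/0.462 = 0.325, or about 32% of the control mean. The paragraph is internally consistent on these terms.

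**3. Carry that d to one value per centre.** With 26 vs 26 (50 df) and a centre-level SD equal to the implied educator-level SD, power is 37% (38% by the normal approximation at d = 0.459).

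**4. Vary the SD.** The equal-SD assumption is not in the document. If r is the ratio of the centre-value SD to the educator-report SD, the standardised difference is 0.462/r:

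| r | d | Power, 26 vs 26 |
|---|---|---|
| 0.6 | 0.77 | 78% |
| 0.7 | 0.66 | 65% |
| 0.8 | 0.58 | 53% |
| 1.0 | 0.46 | 37% |
| 1.2 | 0.38 | 28% |

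A ratio near 0.6 is what the protocol's own ICC gives for the mean of three educator reports: √(1.06/3) = 0.594.

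**5. Allow for baseline adjustment.** With baseline–follow-up correlation ρ, the residual SD falls by √(1 − ρ²). At r = 1.0:

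| ρ | d | Power |
|---|---|---|
| 0.5 | 0.53 | 47% |
| 0.7 | 0.65 | 63% |
| 0.8 | 0.77 | 78% |

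**6. Detectable effect at centre level.** With 26 vs 26 and 80% power this is 0.79 SD, in units of the centre-value SD and whatever that SD is. At r = 1.0 it is 0.79 × 0.325 = 26% of the control mean. With baseline adjustment at ρ = 0.5 it is 0.79 × √0.75 = 0.69 SD.

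**7. Sensitivity of the self-report calculation to the ICC.** Keeping d = 0.462 and 79 educators per arm at 79/26 per centre:

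| ICC | Design effect | Power |
|---|---|---|
| 0.03 | 1.06 | 80% |
| 0.1 | 1.20 | 75% |
| 0.3 | 1.61 | 62% |
| 0.5 | 2.02 | 52% |

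**The case against.** **The sentence may refer only to self-report.** It counts educators, and the section calls these educator outcomes. This stands: for that source the 80% follows from the stated ICC. But the section does not say so, and it offers no calculation for the other source of the same primary outcome.

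**A reader might infer that the trial has 37% power for its observed outcome.** The documents do not support that as a flat statement. It requires a centre value to vary as much as a single educator's report, and no SD is given for either. A full day's observation may average over staff and activities and so vary less; at a ratio of 0.6 power is close to the stated 80%. The outcomes are also collected at baseline, and adjustment for baseline would help. However, nothing in the document establishes a ratio as low as 0.6 or a correlation as high as 0.8, so the 80% is not shown for this measure either.

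**A reader might extend the 37% to the best-practice index.** It does not extend. The 0.46 SD was back-solved from a 15% change in minutes and has no meaning for a count of practices. Only the 0.79 SD detectable effect applies to the index, because it is one value per centre.

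**One observed record per centre is inferred.** The article does not say so outright, and a full protocol might describe records by room. It is a strong inference from how the observation is described; for the index, the facility level is explicit.

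**The ICC of 0.03 may be sound.** It comes with a cited source that is not available here. Educators in one centre probably report on a shared schedule, which argues for a higher value, but that is judgement. It justifies a range, not a claim that 0.03 is wrong.

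**Nothing is miscalculated.** Agreed. The fault is a mismatch between the unit used for sizing and the level of one of the two measures.

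**Conclusion.** The point holds in limited form. The stated 80% power belongs at most to educator self-report of AP minutes. For observed AP minutes the sample, as described, is 26 vs 26 centres, and the document gives no basis for the 80%. Unadjusted power for the 15% difference is about 37% if centre values and educator reports have equal SDs, and between about 78% and 28% over SD ratios of 0.6 to 1.2. With baseline adjustment at ratio 1.0 it is about 47% to 78% for correlations of 0.5 to 0.8. These figures rest on the back-solved 0.46 SD, a two-sided 5% test and one record per centre per visit. The firmer result is the detectable effect: 0.79 SD at 80% power for any outcome with one value per centre, the facility index included, before baseline adjustment.

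**What to change.** In the Sample size calculation section:

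- Limit the sentence on 79 educators, 15% and 80% power to educator self-report, and show its power over a range of ICCs (about 75%, 62% and 52% at 0.1, 0.3 and 0.5).
- State which source supplies the powered AP-minutes endpoint, with the mean and SD assumed for it.
- Add that, for centre-level outcomes (observed measures and the facility index), 26 vs 26 centres give 80% power for about 0.79 SD, or about 0.69 SD with baseline adjustment at correlation 0.5. If an SD for observed minutes is available, express this also in minutes or per cent.

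No centres are added, and neither the design nor data collection changes. The cost is a less favourable stated figure for the observed outcome.

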### Data analysis

A hierarchical mixed effect model incorporating both fixed and random effects at the ECEC and child levels will test the impact of ATP+ on the primary and secondary outcomes, while accounting for the clustering of children, educators, and managers within ECEC centres). Following intention-to-treat principles, several analyses will be conducted with each of the primary and secondary outcomes. The corresponding levels of policy and practice variables will be used as the main independent variables, with child-level demographic variables (age, sex) included as covariates. Missing data patterns will be examined to determine proper imputation techniques to use before or during data analysis (e.g., multivariate normal imputation, chained equations, etc.).

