### Study aim and hypothesis

The purpose of this research is to investigate whether the enhanced training and resources to support the use/application of facility-level implementation strategies: 1) increases adherence to the BC Directors of Licensing Standard of Practice for AP, and 2) improves 2.5-5.9-year-old children’s FMS. It is hypothesized that centres randomised to the ATP+ intervention will, in comparison to those assigned to the waitlist control group, have greater adherence to the AP standard (time spent in and number of AP, FMS, and outdoor activities), and consequently children attending intervention centres will have greater improvements in their FMS scores over the intervention period. Secondary outcomes will include change in characteristics of providers (skills, self-efficacy, commitment to change), organizational processes (actions to prioritize AP and FMS), and in the environment. It is hypothesised that changes in the secondary outcomes will be higher in centres exposed to the ATP+ intervention as compared to those assigned to the waitlist control group.

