### Data collection

All study outcomes will be collected at baseline and at follow-up, approximately three months later. This will be post-intervention for the experimental group and prior to the intervention for the waitlist control group.

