### Secondary outcomes

***EPAO-SR tool***: This instrument will also capture: a) change in the characteristics of the providers (educators and managers) including skills, self-efficacy, and commitment to change facility practices to implement the AP standard; and b) changes in organizational processes implemented by managers including actions to prioritize AP (such as establishing a champion, modifying policies, setting goals and routines, routinizing processes, monitoring, etc.); and c) changes in the environment such as modifying the indoor or outdoor environment to support AP and FMS.

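### The analysis section names policy and practice levels, not randomised allocation, as the main independent variables, which contradicts its own intention-to-treat test of ATP+

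*Protocol article*

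**What the plan says.** The Data analysis section opens with a hierarchical mixed model that "will test the impact of ATP+ on the primary and secondary outcomes". It then states: "Following intention-to-treat principles, several analyses will be conducted with each of the primary and secondary outcomes". The next sentence fixes the predictors: "The corresponding levels of policy and practice variables will be used as the main independent variables", "with child-level demographic variables (age, sex) included as covariates". No arm, group, time or arm-by-time term is named.

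Four other parts of the article bear on this:

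- **Study aim and hypothesis** is a comparison of randomised groups: "centres randomised to the ATP+ intervention will, in comparison to those assigned to the waitlist control group, have greater adherence to the AP standard". It presents the gain in children's fundamental movement skills (FMS) as a result of that adherence.
- **Primary outcomes** makes practice itself an outcome, including "an index on the number of best practices facility adheres to".
- **Secondary outcomes** includes policy change among the organisational processes: "establishing a champion, modifying policies, setting goals and routines, routinizing processes, monitoring, etc".
- **Data collection** sets the timing: "All study outcomes will be collected at baseline and at follow-up, approximately three months later".

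**The concern.** An intention-to-treat estimate compares centres as they were allocated. A coefficient on a centre's level of policy or practice does not do that. Centres were not randomised to practice levels, so the coefficient can reflect anything that makes a centre both better at active play and home to more skilled children, such as staffing, space or family background.

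Two errors become possible if the sentence is followed. An association between practice and FMS could be reported as an effect of ATP+ when ATP+ did nothing. Or a real effect of ATP+ could be missed, because it does not run through the measured practices or because the model adjusts for the route by which it acts. This concerns the test of the primary hypotheses, so a reader could not tell whether a reported result is randomised evidence.

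**Working it through.** No stated figure is in dispute; the check is of the model against the question it is meant to answer.

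**1. What the trial was sized for.** The Sample size calculation gives 79 educators per group in 26 centres, ICC 0.03 and design effect 1.06. This reproduces: 79/26 = 3.04 educators per centre, and 1 + (3 − 1) × 0.03 = 1.06. The target is a 15% improvement relative to control. The child calculation (0.5 SD, 92 per group) is also per group. Both are comparisons between arms.

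**2. What the named predictor estimates under each reading.** The section does not say which measurement occasion supplies the levels.

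| Levels meant | Allocation not in model | Allocation entered beside them |
|---|---|---|
| Follow-up | Non-randomised association | Arm coefficient omits whatever passes through practice |
| Baseline | Non-randomised association | Arm coefficient is valid, but is not named as the main term |

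**3. The follow-up reading in algebra.** Let practice P = a·arm + error and FMS = c·arm + b·P + error, with no shared causes of P and FMS. The total ATP+ effect is c + ab; the arm coefficient adjusted for P is c.

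- Full mediation, a = 1, b = 0.5, c = 0: total 0 + 1 × 0.5 = 0.50 SD; adjusted 0.00. This follows from the assumption and is not a forecast.
- Partial mediation, a = 1, b = 0.25, c = 0.25: total 0.25 + 0.25 = 0.50; adjusted 0.25.
- No mediation, a = b = 0, c = 0.5: adjusted 0.50, but a model with practice alone has a practice coefficient of 0 and misses the effect.

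**4. False-positive rate of a practice-level test.** None of these inputs is a document value for child FMS, except that 52 is the planned number of centres. Assumed: 4 analysed children per centre; neither ATP+ nor practice affects FMS; practice correlates ρ with the centre's underlying FMS level. ICC 0.03 is borrowed from the educator calculation; 0.10 is a second assumed value.

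The correlation between practice and the observed centre mean is r = ρ × √[ICC / (ICC + (1 − ICC)/4)]. With z = atanh(r) × √(52 − 3), the two-sided 5% test rejects with probability of about Φ(z − 1.96) + Φ(−z − 1.96).

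Example, ICC 0.03 and ρ = 0.5: r = 0.5 × √(0.03/0.2725) = 0.166; z = 0.1675 × 7 = 1.17; rejection about 0.216. Simulation of 20,000 trials per cell, using regression on centre means, agrees:

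| ICC | ρ | r | Formula | Simulated, practice | Simulated, arm |
|---|---|---|---|---|---|
| 0.03 | 0.1 | 0.033 | 0.056 | 0.054 | 0.049 |
| 0.03 | 0.2 | 0.066 | 0.075 | 0.075 | 0.054 |
| 0.03 | 0.3 | 0.100 | 0.108 | 0.107 | 0.051 |
| 0.03 | 0.5 | 0.166 | 0.216 | 0.218 | 0.051 |
| 0.10 | 0.1 | 0.055 | 0.067 | 0.069 | 0.050 |
| 0.10 | 0.2 | 0.111 | 0.122 | 0.123 | 0.052 |
| 0.10 | 0.3 | 0.166 | 0.217 | 0.218 | 0.051 |
| 0.10 | 0.5 | 0.277 | 0.513 | 0.518 | 0.050 |

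Smaller simulations put the last practice cell at 0.52 to 0.53.

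**5. The practice outcomes.** If the sentence covers every outcome, as the sentence before it suggests, follow-up practice would be both outcome and predictor. With baseline levels the same term would be an ordinary baseline adjustment.

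**The case against.** The best defence is that an arm term is implied. The section says the model tests the impact of ATP+, the Randomization section conceals allocation from the researchers at the analysis stage, and the hypotheses and sample size are between groups. The Introduction also notes that the link between staff practices and child-level outcomes has not been studied. Pairing practice variables with child age and sex fits an additional child-level model among the several analyses promised. The phrase about corresponding levels might even refer to levels of the hierarchy. And a journal article condenses the full plan.

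Much of this stands, and it limits the point. A reader might infer that the randomised arm is dropped altogether, that the predictors are certainly measured after randomisation, or that practice is certainly regressed on itself. The documents support none of these as fact: no arm term is excluded, the measurement occasion is not given, and the sentence may mainly concern child outcomes. Nor do they support a single inflated error rate; the value near one half belongs to the least favourable assumptions in the table.

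What does not stand is that the wording is harmless. Condensing explains an omission; it does not explain naming a different variable as the main one directly after claiming intention to treat for all primary and secondary outcomes. Studying practice and child skills is a legitimate aim, but it is a separate analysis.

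**Conclusion.** The sentence is wrong as written and must be corrected. The section contradicts its own aim and intention-to-treat statement, and the article's hypotheses and sample size, about what the main independent variable is. This rests on the text alone. It is a finding about the specified model, not about what the authors intended.

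The consequences are conditional. The loss of the total ATP+ effect requires follow-up levels and some mediation through practice. The circularity requires follow-up levels and a sentence that applies to the practice outcomes. Under the baseline reading neither arises, yet allocation is still not the main term. The inflation of false positives, about 5–22% at ICC 0.03 and 7–52% at ICC 0.10 against a nominal 5%, depends on assumed confounding. It shows the direction; its size in this trial is unknown.

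**What to change.** Replace the sentence on main independent variables with text such as:

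> Randomised allocation (ATP+ versus waitlist, as assigned) is the main fixed effect in the model for every primary and secondary outcome, with a random effect for centre and adjustment for the baseline value of that outcome. Policy and practice levels measured at follow-up are not entered as predictors in these models.

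An arm-by-time term in a repeated-measures model is an acceptable alternative to baseline adjustment, since the outcomes are changes measured twice; it then also needs a random effect for the child or staff member. Child age and sex can stay as covariates in the child models.

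Describe the practice-to-FMS models separately as exploratory mediation or association analyses, stating which measurement occasion is used. The cost is a few sentences in the protocol or analysis plan, best settled before allocation is revealed to the analysts. No new data are needed, and the sample size does not change because it was already calculated between arms.

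### The analysis model names child age and sex as covariates for outcomes worded as change, but not the baseline value of the outcome; adjusting for it would gain precision at almost no cost.

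*Protocol article*

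**What the plan says.** - Data collection: "All study outcomes will be collected at baseline and at follow-up, approximately three months later". A baseline value is therefore planned for every outcome.
- Primary outcomes: the first is titled "Change in AP and FMS practices", and the child motor-skill outcome is likewise titled as a change. Study aim and hypothesis: "Secondary outcomes will include change in characteristics of providers", followed by organisational processes and the environment.
- Data analysis: "A hierarchical mixed effect model incorporating both fixed and random effects at the ECEC and child levels will test the impact of ATP", that is, of ATP+, on the primary and secondary outcomes. On the predictors it says: "The corresponding levels of policy and practice variables will be used as the main independent variables", "with child-level demographic variables (age, sex) included as covariates".

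The section does not define the dependent variable and does not say how the baseline measurement enters the model.

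**The concern.** Where the same quantity is measured before randomisation and again at follow-up, the baseline value is usually the most useful covariate available. Here a covariate set is stated, and it leaves that value out.

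The set also fits only part of what it is applied to. Age and sex of a child can be entered for the FMS score. They do not describe a centre's observed minutes of active play, an educator's self-efficacy or a manager's organisational actions. For those outcomes the section names no adjustment covariate that applies.

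Three analyses fit the wording as it stands: the change score, the follow-up value alone, or a repeated-measures model with an unconstrained arm-by-time term. Each is less precise than an analysis that adjusts for baseline. The loss would fall on a trial of 26 centres per arm, in which some practices are recorded by field observation at centre level.

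**Working it through.** **The plan's own figures.** The article states no variance reduction, so the first check is whether its sample size uses a baseline correlation.

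- Educators: "A sample of 79 educators per group, within 26 ECEC centres would be sufficient to detect a 15% improvement relative to control in AP minutes", with ICC 0.03 and design effect 1.06. With 79/26 = 3.04, or about 3, educators per centre, 1 + (3 - 1) x 0.03 = 1.06. This reproduces. The 79 cannot be fully checked because no mean or SD of AP minutes is given.
- Children: 0.5 SD, 80% power, alpha 0.05 (two-sided assumed). n = 2 x ((1.960 + 0.842)/0.5)^2 = 62.8 per group. Carrying over the educator ICC of 0.03 (an assumption) and allowing for 25% attrition:
  - 5 children per centre: 62.8 x 1.12 / 0.75 = 94.
  - 3.75 children per centre (5 x 0.75): 62.8 x 1.0825 / 0.75 = 91.

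The stated 92 lies between these two. It is obtained, near enough, without any baseline correlation, so the documents supply no value of rho.

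**Variance under each analysis.** Set the SD to 1 at both times (assumption) and let rho be the baseline to follow-up correlation (assumption, range shown). Per unit:

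- follow-up only: 1
- change score: 2(1 - rho)
- baseline-adjusted: 1 - rho^2

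The ratio of adjusted to change score is (1 - rho^2) / (2(1 - rho)) = (1 + rho)/2, so the reduction is (1 - rho)/2. Against follow-up only the reduction is rho^2. With complete data at two time points, an unconstrained arm-by-time term gives the same estimate as the change score.

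| rho | change score | follow-up only | adjusted | cut vs change score | cut vs follow-up only |
|---|---|---|---|---|---|
| 0.3 | 1.40 | 1.00 | 0.91 | 35% | 9% |
| 0.5 | 1.00 | 1.00 | 0.75 | 25% | 25% |
| 0.7 | 0.60 | 1.00 | 0.51 | 15% | 49% |
| 0.9 | 0.20 | 1.00 | 0.19 | 5% | 81% |

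**Check under clustering.** A simulation with 26 centres per arm, 5 children per centre and ICC 0.03 gave reductions against the change score of 34.9%, 23.2%, 15.2% and 5.1% at the same four values of rho. The formula therefore holds well in a design of this shape.

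**Unequal SDs.** If the baseline SD is k times the follow-up SD, the change-score variance is 1 + k^2 - 2k x rho. At rho 0.3, 0.5 and 0.7 the reduction against the change score is:

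- k = 0.8: 22%, 11% and 2%
- k = 1.25: 50%, 43% and 37%

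**The case against.** The strongest objection is that this is a condensed article and the analysis plan is not shown. How baseline is parametrised is commonly left to that plan, and nothing in the article rules out baseline adjustment. That argument has force against a complaint of mere silence. It has less force here, because the article does name covariates, applies them to all outcomes, and names ones that cannot apply to several of them.

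Four stronger readings are tempting, and the documents do not support them.

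- *Change scores are what will be analysed.* A title worded as change names an outcome; it does not fix the dependent variable. Random effects at child level point, if anything, towards repeated measures, since with one change score per child such an effect could not be separated from the residual. If that model constrains baseline means to be equal across arms, it is about as efficient as baseline adjustment and there is next to nothing to gain.
- *The variance would fall by 15 to 35%.* That range needs rho between 0.7 and 0.3 and equal SDs. The documents give neither.
- *The treatment estimate would be biased.* Under randomisation, change-score, follow-up-only and baseline-adjusted analyses are all unbiased. Chance baseline imbalance bears on precision, not on validity.
- *Centre-level outcomes are badly underpowered because baseline is left out.* A standardised effect of about 0.46 can be back-calculated from the educator numbers (79/1.06), but it is on the educator scale. Applying it to one value per centre assumes the same SD at both levels, which the article does not say, and any low power that results comes mainly from that switch of unit.

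**Conclusion.** The point holds as a matter of precision and of fixing the analysis in advance. The stated covariate set leaves out a prognostic variable that is already being collected for every outcome, and the covariates it does name do not apply to centre, educator or manager outcomes.

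The size of the gain is conditional on which analysis is meant and on rho. With equal SDs and rho strictly between 0 and 1, it is positive against either a change-score (or unconstrained arm-by-time) analysis or a follow-up-only analysis. Which comparator loses more depends on rho: the change score when rho is low, follow-up only when rho is high, and the two are level at 0.5. Only a model that already uses baseline efficiently would gain nothing, and the article does not describe one. Because the remedy is so cheap, it is worth adopting without knowing rho.

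**What to change.** In the Data analysis section, and in the analysis plan, state that:

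- the follow-up value of each outcome is modelled on randomised arm and the baseline value of the same outcome, with the centre-level baseline for centre outcomes and the participant's own baseline for child, educator and manager outcomes; or, equivalently, that a mixed model of both time points is used with baseline means constrained to be equal across arms;
- the centre random effect is kept;
- child age and sex enter the model for the FMS outcome only.

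Region and season of measurement are optional additions. Recruitment is "from the Metro Vancouver and Greater Victoria regions of BC, Canada" and follow-up comes about three months after baseline, so both would be known, but the case for them is weaker and the fix does not depend on them.

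The cost is a few sentences and about one degree of freedom per model. No new data are needed.
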